### Objectives

The main objectives of this exploratory, hypothesis-generating trial are to (1) assess whether improvements in sleep architecture (e.g., SWS, REM sleep), total sleep time, and sleep quality (e.g., increased sleep efficiency, decreased sleep onset latency and restlessness [restless bouts/hour]) are associated with improved cognitive performance and biomarker panels for brain and cardiometabolic health; (2) evaluate the effects of structured, moderate-level aerobic and anaerobic exercise on cognitive performance and biomarker panels for brain and cardiometabolic health; (3) examine the combined, potentially synergistic effects of the sleep and exercise interventions on cognitive performance and biomarker panels for brain and cardiometabolic health; and (4) investigate the role of light exposure as a potential modulator of sleep parameters.

The central hypotheses of this trial are that (1) disrupted baseline sleep architecture, short and long durations, and lower sleep quality measures as well as less physical activity will be linked with poorer cognition and more adverse brain and cardiometabolic biomarker profiles at baseline; (2) improvements in sleep metrics (i.e., increased sleep efficiency, SWS, REM, and total sleep time, as well as reduced onset latency and restlessness) will independently correspond to cognitive improvements and favorable biomarker changes during the 8-week intervention; (3) increased exercise will be independently associated with better cognitive, brain, and cardiometabolic health; (4) the combined sleep and exercise group will demonstrate greater improvements in cognitive function and biomarker profiles for brain and cardiometabolic health; and (5) these changes will be more pronounced in individuals with MCI compared to age- and sex-matched, cognitively normal (CN) controls. Given the short trial duration, this trial is explicitly intended for signal detection, building on similar 8-week studies of lifestyle-based behavioral interventions that have successfully detected early cognitive and physiological response patterns.

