#### Participant recruitment

A total of 60 participants comprised of approximately 30 CN older adults and 30 older adults with MCI will be enrolled in this study. Recruitment strategies will consist of a combination of the following:Participants will be recruited from existing studies and research registries maintained by the Translational Sleep and Circadian Sciences (TSCS) Laboratory at the University of Miami Miller School of Medicine. All individuals considered for enrollment will have previously consented to be contacted for future research opportunities. Initial contact will be made via phone by trained study personnel to confirm interest and screen for eligibility.In addition, recruitment will include referrals for prospective participants with an MCI diagnosis from the Division of Cognitive Neurology at the University of Miami.Moreover, flyers and social media advertisements will be distributed throughout southern Florida to further aid in recruitment efforts.This trial will participate in the University of Miami’s Consent to Contact program, which allows approved researchers to access a database of University of Miami Health System patients who have agreed to be contacted about participating in clinical research studies.

Recruitment and enrollment procedures will comply with all institutional and federal guidelines, including the Health Insurance Portability and Accountability Act (HIPAA), to ensure privacy and confidentiality of all protected health information that is obtained. Eligible participants will be equally randomized (*n* = 20 per group) into three study arms: sleep-only, exercise-only, or combined sleep and exercise. Stratified randomization by cognitive status will be employed to ensure balanced representation across groups (i.e., each group will be comprised of 10 CN participants and 10 participants with MCI).

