#### Adherence and engagement

In order to assess adherence to the exercise sessions, attendance will be recorded for all in-person sessions, and wearable devices (Fitbit) will track daily physical activity, including steps, heart rate, and durations of physical activity. Weekly check-ins (10–15 minutes) via phone or secure teleconference will be conducted and documented to ensure protocol adherence, troubleshoot technical issues, and maintain engagement. All data will be stored in HIPAA-compliant systems. Fitbit and the Digital Neuro-Signature Platform data will be de-identified and linked using secure participant codes. Statistical models will include age, sex, years of educational attainment, employment status (unemployed/employed), socioeconomic status, baseline sleep metrics, baseline physical activity levels, and cognitive status as covariates. By integrating standardized, in-lab exercises, wearable technology, digital cognitive assessments, and multimodal biomarker data, this arm of the *CASE* study aims to explore the cognitive, brain, and cardiometabolic impacts induced by structured exercise in aging adults who are at higher risk for AD using a real-world, ecologically valid framework.

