Primary group comparisons will be conducted using LMMs, which offer flexibility for handling repeated measures, unbalanced data, and missingness under the Missing at Random assumption. Each LMM will include fixed effects for group (sleep, exercise, combined sleep + exercise), time (baseline, 8-week follow-up), and the interaction term between group × time. Subject-specific random intercepts will be included to account for intra-individual correlation over time. The main test of intervention efficacy will be the group × time interaction term. To evaluate whether improvements in biomarkers (e.g., HbA1c, hs-CRP) moderate the effects of the interventions on cognitive outcomes, exploratory moderation models will be conducted. These models will include biomarker change scores, group assignment, and group × biomarker interaction terms as predictors of cognitive change. Moderation models will use PROCESS v5.0 Macro for SPSS with bias-corrected bootstrapping (5,000 resamples). Significant interactions will be probed using Johnson-Neyman techniques.

Given the small sample size, power for detecting small effects will be limited. Thus, all models will report estimated effect sizes (Cohen’s *d*, partial *η*^2^), 95% confidence intervals, and significance levels (*α* = 0.05). No corrections for multiple comparisons will be applied to primary outcomes; however, for secondary and exploratory outcomes, a Benjamini–Hochberg false discovery rate (FDR) correction will be used to control for Type I error. Composite indices may be created to reduce variable dimensionality. For cognitive outcomes, domain-specific cognitive function scores will be z-scored and aggregated into a global composite score. For blood-based biomarkers, z-scored values will be averaged to create an overall plasma-based AD risk index as well as a cardiometabolic risk index for all subjects.

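### Central hypothesis 5 (larger changes in MCI than in cognitively normal participants) is not estimated by any model term the plan states, and the stratification factor does not act on change

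*Protocol article*

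**What the plan says.** The Objectives section lists five central hypotheses. The fifth is that "these changes will be more pronounced in individuals with MCI compared to age- and sex-matched, cognitively normal (CN) controls". The design provides for this comparison. Under Participant recruitment, "Stratified randomization by cognitive status will be employed to ensure balanced representation across groups", and "each group will be comprised of 10 CN participants and 10 participants with MCI".

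The Analysis plan gives the terms of each primary model: "fixed effects for group (sleep, exercise, combined sleep + exercise), time (baseline, 8-week follow-up), and the interaction term between group × time". It adds that "Subject-specific random intercepts will be included to account for intra-individual correlation over time" and that "The main test of intervention efficacy will be the group × time interaction term". Cognitive status enters the models in one other place, Adherence and engagement (exercise-only arm), where the statistical models are to include, among other variables, "baseline sleep metrics, baseline physical activity levels, and cognitive status as covariates".

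Several moderators and interactions are named, but none is MCI/CN status acting on change:

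- Analysis plan: group × biomarker change, in the moderation models.
- Biomarker collection strategy (exercise-only arm): baseline plasma pathology.
- Self-reported physical activity: discrepancy scores between questionnaires and Fitbit. Cognitive status is mentioned here, but only in connection with those scores.
- Limitations: expectancy ratings.
- Analysis strategy (combined arm): sleep and exercise main effects and their interaction.
- Discussion: light exposure.

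**The concern.** Hypothesis 5 is about how change differs between two kinds of participant. A model can address it only if some term lets change depend on cognitive status, and no stated term does. A reader may take the covariate entry as covering it, but a covariate main effect describes a difference in level, not in change.

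Two things are at stake. First, one of the five central hypotheses would reach the analysis with no prespecified estimate, so the form of the comparison would be chosen after the data are seen. Second, the factor used to stratify randomisation would play no part in the variance of the main test. Any MCI–CN difference in mean change would stay in the error term.

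**Working it through.** **The plan's own figure.** The article gives no power or precision figure for hypothesis 5. Its 60–65% power refers to group × time only. On the simplest reading (f² = 0.25 on the change score, λ = 60 × 0.25 = 15, F with 2 and 57 df) I get 93%, so the figure does not reproduce that way. That is a separate matter, and nothing below uses the figure.

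**Step 1. What a status main effect does with complete data.** Write the model for participant *i* at visit *t* (0 or 1) as

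y_it = α_g + β_g·t + γ·status_i + b_i + e_it.

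The change is y_i1 − y_i0 = β_g + (e_i1 − e_i0). Both γ·status_i and b_i cancel. With both visits observed and a between-subject variance estimated above zero, the group × time estimate is the difference in mean change, and its standard error comes from the within-person residuals. Neither depends on γ.

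**Step 2. Check by fitting.** Simulated trials had 20 per arm (10 CN, 10 MCI). The values are assumed: intercept SD 0.8, residual SD 0.6, MCI 1.0 lower at both visits, mean change 0.2, plus 0.3 (CN) or 0.6 (MCI) in the combined arm. Random-intercept models were fitted with and without a status main effect, in 40 trials per row. The shift is in the combined-arm group × time estimate.

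| Nominal missing follow-up | Mean absolute shift | Largest shift | Typical SE |
|---|---|---|---|
| 0% | 0 (to rounding) | 3 × 10⁻¹⁵ | 0.30 |
| 15% (CN 7.5%, MCI 22.5%) | 0.02 | 0.09 | 0.32 |
| 30% (CN 15%, MCI 45%) | 0.03 | 0.11 | 0.33 |

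The SE itself moved by at most 0.004 and 0.009 in the two missing-data rows. So the cancellation is exact for complete data and approximate otherwise. In every row γ remains a difference in level and says nothing about a difference in change.

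**Step 3. Precision of the terms that would address hypothesis 5.** Unit: within-cell SD of change, which the article does not give. Full follow-up of 60 participants, with 10 per arm-by-status cell.

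- Arm contrast (20 vs 20, 57 df): t × √(1/20 + 1/20) = 2.002 × 0.316 = ±0.63 SD.
- Status × time, all arms pooled (30 vs 30, 54 df): 2.005 × √(1/30 + 1/30) = 2.005 × 0.258 = ±0.52 SD.
- MCI-minus-CN difference in one arm contrast (four cells of 10, 54 df): 2.005 × √(4/10) = 2.005 × 0.632 = ±1.27 SD.

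The standard error of the last is √(4/10) / √(2/20) = 2 times that of the arm contrast.

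**Step 4. What status × time would gain for the main test.** If MCI and CN differ by δ within-stratum SDs in mean change, the share of change variance removed is (δ²/4)/(1 + δ²/4). The article gives no δ, so this range is assumed:

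- δ = 0: nothing removed, and 1 df spent.
- δ = 0.5: 0.0625/1.0625 = 6%, so the SE falls by about 3%.
- δ = 0.8: 0.16/1.16 = 14%, SE about 7% lower.
- δ = 1.0: 0.25/1.25 = 20%, SE about 11% lower.

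In one further simulated 60-participant dataset, status and age main effects left the SE at 0.2599, and adding status × time reduced it to 0.2522, which is 3%.

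**The case against.** The best defence is that the sentence listing the model terms introduces the primary group comparisons, and the MCI–CN contrast is not one of those. A journal article may leave models for further hypotheses to a full analysis plan, which is not shown. The trial is also described as exploratory, with emphasis on effect sizes and intervals. This lowers the weight of the point but does not remove it. The hypothesis is labelled central, the design stratifies for it, and the article describes in detail a biomarker moderation analysis while giving none for MCI status.

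Four stronger readings are tempting, and the documents do not support them:

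- *Status as a covariate can never affect the group × time estimate.* That is exact only for complete data. The plan expects incomplete follow-up and uses maximum likelihood, and status could also act in the ANCOVA fallback.
- *The trial will compare p-values from separate MCI and CN analyses.* Nothing in the article proposes this, so the errors of that practice cannot be counted as a harm of the plan. A sentence ruling it out is only a precaution.
- *Group × status × time is the one proper test.* All three arms are active. If every intervention helped MCI participants more by the same amount, the three-way term would be zero although hypothesis 5 was true. The wording maps first to status × time.
- *Every listed covariate should be interacted with time.* That would spend several df in 60 participants, and it is a debatable trade-off rather than a correction.

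**Conclusion.** The point holds as a mismatch between a stated central hypothesis and the stated models. No term estimates an MCI–CN difference in change, and the stratification factor does not act on change. It does not bias the main test. With complete data the group × time estimate is the same with or without the status main effect. In the simulations with missing follow-up the shift was at most 0.11 against a standard error of about 0.3.

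The conclusion rests on reading cognitive status as a covariate to mean a main effect, which is the ordinary meaning but is not spelled out. The half-widths assume full follow-up and equal cells. The gain in precision for the main test depends on an MCI–CN difference in mean change that the documents do not give. It may be only a few percent, or nothing.

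Even with the right terms, the trial can estimate hypothesis 5 only roughly: ±0.52 SD for the overall difference in change and ±1.27 SD for a difference in an arm contrast. The change should be made because it is cheap and aligns the model with the hypothesis, not because it would give a decisive answer.

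**What to change.** 1. Add cognitive status × time, with the status main effect, to each primary linear mixed model, so that the stratification factor acts on change.
2. State that hypothesis 5 is exploratory and will be reported as estimates with 95% confidence intervals: status × time for the overall MCI–CN difference in change and, in a separate model, group × status × time for whether arm differences vary by status.
3. State the limit of the first estimate: without an untreated arm, status × time mixes intervention response with practice effects and natural change.
4. State that no claim about MCI versus CN will rest on separate p-values in the two strata.

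Cost: one degree of freedom in each primary model, one additional exploratory model per outcome, and no new data. The three-way intervals will be wide and should be reported as such. The other covariates can stay as they are.

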#### Baseline and follow-up visits

Data will be collected at baseline, biweekly, and at the 8-week follow-up to assess changes in sleep, exercise, biomarkers, and cognition. After consent and randomization, participants will be onboarded in person to each intervention-specific device and observed for a 7-day period prior to the baseline visit to establish baseline sleep patterns and/or physical activity levels relevant for each assigned intervention and to ensure all eligibility criteria are satisfied. Cognitive function will be measured using an augmented reality-based tool at baseline and week 8, with brief pulse assessments administered twice-weekly throughout the intervening period. Blood biomarkers will be collected via venipuncture at Quest Diagnostics (baseline and week 8). Physical activity and sleep data will be respectively monitored using Fitbit (all groups) and the Elemind headband (sleep and sleep + exercise groups), and light exposure will be tracked via the Lys device (sleep and sleep + exercise groups). Participants will also complete validated self-report surveys (e.g., PASE, CHAMPS–MET, PROMIS instruments) to capture psychosocial and behavioral variables at weeks 0 and 8. This multimodal approach will enable temporally-aligned, comprehensive data capture across digital and self-reported domains (see Table 3).

**Table 3 Tab3:** Timeline of questionnaires provided

Variable	Screening	Baseline	8-week
Basic Info Screening Form (eligibility criteria)	X		
Physical Activity Readiness Questionnaire (PAR-Q)	X		
Quick Mild Cognitive Impairment screen (QMCI), 6-item	X		
Demographic Questionnaire		X	
Chronic Health Questionnaire		X	X
PROMIS Self-reported Cognitive Functioning Behaviors Short Form		X	X
PROMIS Sleep Disturbance 4a		X	X
PROMIS Emotional Support 4a short form		X	X
PROMIS Depression 4a shot form		X	X
PROMIS Anxiety 4a short form		X	X
PROMIS Social Isolation 4a		X	X
General PROMIS Life Satisfaction 5a		X	
Cross Ethnic-Racial Identity Scale		X	
PASE Physical Activity Questionnaire (exercise and sleep + exercise interventions only)		X	X
CHAMPS-MET Physical Activity Questionnaire (exercise and sleep + exercise interventions only)		X	X

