**Biomarker data**			
Total cholesterol		X	X
High density lipoproteins		X	X
Low density lipoproteins		X	X
Triglycerides		X	X
High-sensitivity C-reactive protein		X	X
Glycated hemoglobin		X	X
C-peptide		X	X
Insulin		X	X
Neurofilament light chain		X	X
Amyloid beta peptide 1–42		X	
Amyloid beta peptide 1–40		X	
Amyloid beta peptide 1–42/amyloid beta peptide 1–40 ratio		X	
Phosphorylated tau at threonine 217		X	

Table outlines the timeline for the collection of information from questionnaires and blood panels. *PROMIS*, Patient-Reported Outcomes Measurement Information System.

Participants who provided written consent and are found to be eligible for participation at the conclusion of the 7-day onboarding screening period will undergo the following procedures in accordance with the intervention to which each subject was assigned:

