#### Limitations

This study will not include a sham stimulation control for the sleep-only group. The decision to forgo a sham condition reflects the real-world, comparative effectiveness design of the CASE study and prioritizes ecological validity over internal blinding. Nonetheless, the absence of participant blinding may introduce potential placebo effects. To address this analytically, expectancy-related influences will be modeled using self-reported perceived benefit measures as an additional covariate in the regression models. Sensitivity analyses will explore whether high expectancy ratings moderate intervention effects. Between-arm comparisons will further contextualize the potential role of non-specific treatment effects in observed outcomes.

In addition, the 8-week interventional period of this clinical trial may not be a sufficient timeframe for detecting significant changes in brain biomarkers; nonetheless, it should be emphasized that the predominant goal of this pilot trial is to identify early trends and signals in these aforestated biomarkers, which will, in turn, inform the design of future, longer-term, fully powered trials. Furthermore, this exploratory approach will enable the assessment of the feasibility and potential effects of each intervention in a relatively small cohort and prefaces more extensive future studies. Notably, the 8-week interventional trial duration was selected based on prior study findings, which showed that behavioral interventions have the capacity to result in early changes in cognitive and physiological measures within a relatively short timeframe [40, 41].

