#### Analysis plan

This study is designed as a three-arm, parallel-group trial comparing the effects of an 8-week exercise intervention (group 1), sleep intervention (group 2), and combined sleep + exercise intervention (group 3) on cognitive performance and biomarkers for brain and cardiometabolic health in older adults with MCI or no cognitive impairment. A total of 60 participants (20 per group) will be enrolled. All analyses will be conducted using IBM SPSS Statistics (Version 31.0.0.0; IBM Corp., Armonk, NY, USA). The primary analytic goal is to determine which intervention arm may demonstrate the greatest improvements in cognitive function and biomarker profiles. Descriptive statistics (means, standard deviations, medians, interquartile ranges, and proportions) will be used to summarize demographic characteristics, intervention adherence, and baseline measures. Primary outcomes will include change**s** in cognitive domain-specific and global cognition scores from the digital cognitive assessments and changes in biomarkers for brain (NfL) and cardiometabolic health (HbA1c, hs-CRP, C-peptide, insulin, total cholesterol, HDL, LDL, triglycerides). Secondary outcomes will include changes in sleep metrics (e.g., sleep efficiency, SWS, REM sleep, and total sleep durations, onset latency, and restlessness, as measured via Elemind) and physical activity/exercise levels (PGE and NPA via Fitbit). Tertiary outcomes will include the role of light exposure (measured via Lys) as a potential modulator of sleep parameters and psychosocial measures (e.g., PROMIS Depression, Social Isolation).

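### The exploratory moderation models, and any model adjusted for perceived benefit rated after exposure, condition on variables the arms can change, so their group and interaction terms are not randomised effects

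*Protocol article*

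**What the plan says.** **Biomarker change.** The Analysis plan gives the aim of the secondary modelling: "To evaluate whether improvements in biomarkers (e.g., HbA1c, hs-CRP) moderate the effects of the interventions on cognitive outcomes, exploratory moderation models will be conducted". It then specifies the model: "These models will include biomarker change scores, group assignment, and group × biomarker interaction terms as predictors of cognitive change". Interactions found significant are to be probed with the Johnson-Neyman technique. The same section lists among the primary outcomes "changes in biomarkers for brain (NfL) and cardiometabolic health (HbA1c, hs-CRP, C-peptide, insulin, total cholesterol, HDL, LDL, triglycerides".

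**Perceived benefit.** The Limitations subsection for Interventional group 2 (sleep only) acknowledges that there is no sham and no participant blinding, and says that "expectancy-related influences will be modeled using self-reported perceived benefit measures as an additional covariate in the regression models". It adds: "Sensitivity analyses will explore whether high expectancy ratings moderate intervention effects". It names no instrument or time point and does not say which regression models are meant.

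**Schedule.** Table 3 is titled "Timeline of questionnaires provided", and its note says: "Table outlines the timeline for the collection of information from questionnaires and blood panels". It has no perceived-benefit or expectancy item at screening, baseline or week 8. Nor does the instrument list under Measures and instruments.

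**Primary model.** The linear mixed model in the Analysis plan has group, time and their interaction as fixed effects, with subject-specific random intercepts. The interaction is the main efficacy test.

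**The concern.** A moderator answers the question of who benefits more, and for that it has to be fixed before treatment can act on it. Biomarker change over the intervention period is a response to the arms. Participants with the same HbA1c fall in two arms are not comparable groups, because each arm selects different people into that stratum. A group term conditional on change is no longer the randomised contrast, and a group × change term need not be effect modification. If the question is whether biomarker improvement accompanies or carries the cognitive gain, that is mediation, and it needs different assumptions.

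Perceived benefit raises the same difficulty if it is rated after exposure. Such a rating can rise with placebo response and also with real improvement, so adjusting for it can remove true effect along with the non-specific part.

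The stake is the pilot's own purpose. The Introduction and the Power and sample size considerations say that its effect sizes and mechanistic findings will inform a larger trial. Estimates from these models should not be carried forward as arm effects or as evidence of differential response.

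**Working it through.** The plan states no figure on this point, so there is none to reproduce. The check is a reading of the text followed by an illustration with assumed inputs.

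**1. Reading the sections together**
- Within the Analysis plan, biomarker change is both a primary outcome of the arms and the moderator of the arms' effect on cognition.
- The Biomarker collection strategy for the exercise-only arm uses the amyloid and p-tau217 markers at baseline only, as covariates or moderators of response. The article thus already applies the sound form to one set of markers.
- The primary mixed model as listed contains neither biomarker change nor perceived benefit.
- Timing: Baseline and follow-up visits says "After consent and randomization, participants will be onboarded in person", with the baseline visit after that, so on this text even a baseline-visit rating follows randomisation. The Randomization section puts completion of the baseline questionnaires first. Only a rating taken before allocation escapes the problem under either order.

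**2. Algebra for the group term**

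Let G be arm (0/1), M the conditioned variable and Y cognitive change, with unit residual SDs:
- M = aG + e_m, Y = tG + e_y, corr(e_m, e_y) = r.
- Within arm, the slope of Y on M is r, so the coefficient on G in the regression of Y on G and M is t − r·a.
- The bias is −a × r, which is zero if a = 0 or r = 0. Its sign depends on the signs of a and r.

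**3. Simulation** (two arms of 20, 2,000 runs per setting, true effect t = 0, M without effect on Y; a and r are assumed)

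| a | r | −a × r | G + M | G + M + G×M | Type I error, G + M |
|---|---|---|---|---|---|
| 0.3 | 0.3 | −0.09 | −0.095 | −0.097 | 6.1% |
| 0.5 | 0.3 | −0.15 | −0.150 | −0.148 | 7.7% |
| 0.5 | 0.5 | −0.25 | −0.241 | −0.257 | 13.0% |
| 0.8 | 0.5 | −0.40 | −0.403 | −0.395 | 25.2% |

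- At a = 0 the conditioned estimate is about 0 for every r. Without M, the model rejects in about 5% of runs in all settings.
- With a true effect of 0.50, conditioning gives 0.357 (a = 0.5, r = 0.3; formula 0.50 − 0.15 = 0.35), 0.258 (a = 0.5, r = 0.5; formula 0.25) and 0.105 (a = 0.8, r = 0.5; formula 0.10).
- Pure mediation (a = 0.5, slope of Y on M 0.3, r = 0): the total effect is 0.5 × 0.3 = 0.15 and the conditioned estimate is 0.00. The model then returns the direct effect, which is not the effect of assignment.

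**4. The interaction term**

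If the residual correlation is r₀ in one arm and r₁ in the other, with unit SDs, the G×M coefficient is r₁ − r₀, even when the treatment effect is the same for everyone. With assumed values 0.3 and 0.5 it is 0.5 − 0.3 = 0.2, with no effect modification present.

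**The case against.** **The efficacy test is untouched.** This stands. A reader might infer that the trial's main arm effects are biased. The documents do not support that: the primary model lists only group, time and their interaction, and the biomarker models are labelled exploratory. One could add that those models aim at the interaction and not the group term. That does not rescue them, because the interaction is not effect modification either (working, step 4).

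**The placebo problem is not ignored.** This also stands. A reader might infer that the covariate is the only remedy offered for having no sham. The Limitations text also plans an expectancy-moderation sensitivity analysis and refers to between-arm comparisons.

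**The timing is unknown.** A reader might take it as given that perceived benefit is rated after treatment starts. The article does not say so. It uses perceived benefit and expectancy ratings for one purpose without a time point. Rating after exposure is the natural reading of the term, but only a plausible one.

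**The article is condensed.** A reader might infer from Table 3 that the adjustment cannot be carried out. The item may be in the full protocol. What the article shows is that an analysis variable it relies on is missing from an otherwise itemised schedule, which is a secondary point.

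**Removing placebo response is the aim.** That is fair, and adjustment may remove some of it. The rating cannot separate that part from real improvement, so the adjusted estimate has no clear meaning.

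**The sizes are assumed.** They are, and the illustration uses two arms where the trial has three.

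**Conclusion.** The point holds within a limited scope. The group and interaction terms of the exploratory biomarker-change models do not estimate randomised effects or true effect modification. The same applies to any model that receives perceived benefit rated after exposure. The primary group × time analysis, as listed, is not affected.

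Neither the size nor the direction of the bias can be derived from the documents. The range in the working, from 0 to −0.40 SD, rests on assumed a and r, unit residual SDs and a linear model. A statement that these analyses would halve a true effect would be one choice of inputs and not a finding. The bias disappears if the arms do not differ on the variable, or if the variable has no link to outcome given arm. Neither can be presumed for markers that are primary outcomes of the interventions.

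**What to change.** 1. **Moderation:** in the exploratory models, replace biomarker change with the baseline biomarker value, as the article already does for the amyloid and p-tau217 markers.
2. **Change scores:** if biomarker change is of interest, present it as an exploratory mediation (association) model and state its assumption of no unmeasured confounding between biomarker change and cognition. Do not report its group term as an intervention effect.
3. **Perceived benefit:** keep any post-randomisation rating out of every model that estimates an arm effect. It can be reported descriptively by arm.
4. **Expectancy:** add one expectancy item, asked for each intervention, to Table 3 at a point before allocation is disclosed. The in-person screening visit after consent would serve under either order of randomisation that the article describes. A rating taken once the participant knows the arm would not do, because in an unblinded trial the assignment itself can shift it. Use the pre-allocation ratings as the covariate or moderator in the sensitivity analysis already planned. Enter the ratings for all interventions, since using only the one for the assigned arm would make the variable depend on allocation again.

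The cost is one REDCap item at an existing visit and revised analysis wording. The limit is that a pre-allocation rating does not capture expectancy that arises after assignment, so the lack of a sham remains a limitation to be stated.
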